### Sample size determination

We plan to examine 40 study participants in the two active arms. This sample size, together with a two-sided α = 0.05, gives 80% power to detect a standardized effect of d = 0.64 with a power of 80%. This effect represents approximately 2.5 points for the general skills scale and approximately 3.5 points for the specific skills scale. As the parameters of the general skills scale range from 1 to 5 and those for the specific skills from 2 to 10, the aforementioned effect would reflect an improvement of exactly one scale unit, which is fairly small. The determination of the sample size for the total scores of general and specific scales can only be estimated, as the correlation between the two scales is unknown. Assuming a positive correlation of *ρ* = 0.5, the standard deviation for the total scores of the scales would be 7.86 for both groups. With the sample size of 40 participants per group and α = 0.05 two-tailed, a difference of 5 points would be detected (for example 3 points for general skills area and 2 points for specific skills area) with a power of 80%. Even smaller differences can be neglected.

In the other analyses, the active study arms are compared with the control group, which consists of students who do not take part in any laparoscopic training. The effect of this control group would be larger than the one of the previous case, thereby allowing for a significantly smaller sample size. In each comparison, a standardized effect of d = 0.79 with 80% power can be measured, which would represent a mean difference of about 6 points on the OSATS scale (for example 3 points for general skills area and 3 points for specific skills area).

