**Methods:**

This is a monocentric, open, three-arm randomized controlled trial. The participants are laparoscopically-naive medical students from Heidelberg University. After a standardized introduction to laparoscopic cholecystectomy (LC) with online learning modules, the participants perform a baseline test for basic skills and LC performance on a virtual reality (VR) trainer. A total of 100 students will be randomized into three study arms, in a 2:2:1 ratio. The intervention groups participate individually (Group 1) or in pairs (Group 2) in a standardized and structured multimodality training curriculum. Basic skills are trained on the box and VR trainers. Procedural skills and LC modules are trained on the VR trainer. The control group (Group C) does not receive training between tests. A post-test is performed to reassess basic skills and LC performance on the VR trainer. The performance of a cadaveric porcine LC is then measured as the primary outcome using standardized and validated ratings by blinded experts with the Objective Structured Assessment of Technical Skills. The Global Operative Assessment of Laparoscopic Surgical skills score and the time taken for completion are used as secondary outcome measures as well as the improvement of skills and VR LC performance between baseline and post-test. Cognitive tests and questionnaires are used to identify individual factors that might exert influence on training outcome.

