### Statistical analysis

The normal distribution provides a fairly exact approximation of the distribution of the scale-specific scores (Figures 1 and two in [46]), which allows standard parametric tests to be used to compare the mean OSATS scores of the three groups [46]. In the first step, overall training effects will be analyzed by a linear mixed model with the main effects Group (1, 2, C), gender (stratification factor), and training pair as a random factor nested in Group 2. If the group effect is not significant at α = 5% in this gatekeeper analysis, statistical inference will stop concluding that there is no substantial training effect at all. If the test is significant, all possible pairs of interventions will be compared (1 vs. C, 2 vs. C, 2 vs. 1) in a similar linear mixed model with group, gender, and training pair (if applicable). These latter analyses will be performed at α = 5% two-tailed, without correction for multiplicity (closed test procedure).

Statistical analysis will be based on the intention-to-treat population that includes all participants that have been randomized and have attended at least one training session. Multiple imputation will be used for missing endpoint information, with linear regression of OSATS scores by the baseline performance on the VR trainer.

Sensitivity analyses will be made using mixed best (Group C) and worst-case (Groups 1 and 2) imputation for the three treatment groups, and vice versa, as well as for the per protocol set of participants that attended all trainings and have complete primary endpoint information.

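### The 80% power for a 5-point difference between individual and paired training is calculated for independent participants, although the planned model treats Group 2 as 20 pairs

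*Protocol article*

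**What the plan says.** The abstract fixes the design: "A total of 100 students will be randomized into three study arms, in a 2:2:1 ratio", that is 40, 40 and 20. The section on sample size determination states that 40 per active arm "gives 80% power to detect a standardized effect of d = 0.64 with a power of 80"%. It then moves to the total OSATS score. "Assuming a positive correlation of *ρ* = 0.5" between the two subscales, "the standard deviation for the total scores of the scales would be 7.86 for both groups", and on that basis "With the sample size of 40 participants per group and α = 0.05 two-tailed, a difference of 5 points would be detected" with 80% power. It dismisses smaller differences as negligible. For the comparisons with control it gives d = 0.79, about 6 points, also at 80% power. Pairing, within-pair correlation and a design effect are not mentioned.

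The statistical analysis section describes a different structure. The gatekeeper model includes "training pair as a random factor nested in Group 2", and the pairwise comparisons, including 2 vs. 1, use a similar mixed model with training pair where it applies.

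**The concern.** The power statement and the analysis model assume different designs. One counts 40 independent trainees in Group 2; the other counts 20 pairs. The Background gives reasons for pairs to be correlated: partners exchange knowledge, discuss technique, analyse errors and learn by watching each other. A power figure with the within-pair correlation set to zero fits neither that rationale nor the model.

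The comparison affected is the one that the Objectives section names as the primary goal. The 5-point figure also serves as the threshold below which differences are said not to matter. The Discussion points out that paired training would let twice as many trainees take part. A non-significant result for 1 vs. 2 could therefore be read as support for pairing, and readers need to know which difference the trial can detect.

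**Working it through.** **Inputs from the protocol article.** Two-sided α = 0.05; 40 per active arm and 20 controls; SD 7.86 in both groups; target 5 points for 1 vs. 2; d = 0.79 for the comparisons with control. Group 2 trains in pairs, so there are 20 clusters of size 2. **Assumed:** the within-pair ICC, which the documents do not give. Adjustment for gender is ignored.

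**1. The plan's own figure.** For independent participants, SE = 7.86 × √(1/40 + 1/40) = 1.758 and d = 5/7.86 = 0.636. The non-central t with 78 df gives power 80.2%. The smallest d detectable with 80% power is 0.634, in line with the quoted 0.64. The stated 80% is therefore the independent-sample result, with no margin for pairing.

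**2. With pairs in Group 2.** The design effect for clusters of two is 1 + (2 − 1) × ICC = 1 + ICC, in Group 2 only:

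SE = 7.86 × √(1/40 + (1 + ICC)/40)

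The df are Satterthwaite-type, combining 39 (Group 1) and 19 (20 pairs). At ICC 0.2, for example, SE = 7.86 × √0.055 = 1.843, df = 47.7 and non-centrality = 5/1.843 = 2.71, so power is 75.7%.

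| Assumed ICC | Power for 5 points | Difference detectable with 80% power |
|---|---|---|
| 0 | 79.7% | 5.02 |
| 0.1 | 77.7% | 5.15 |
| 0.2 | 75.7% | 5.27 |
| 0.3 | 73.8% | 5.39 |
| 0.5 | 70.1% | 5.63 |

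The first row is below 80.2% only because of the smaller df. Simulation on pair means gives 77.5%, 75.6%, 73.6% and 70.0% at ICC 0.1, 0.2, 0.3 and 0.5.

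**3. Group 2 vs. control.** d = 0.79 corresponds to 0.79 × 7.86 = 6.2 points. Under independence, SE = 7.86 × √(1/40 + 1/20) = 2.153, and power is 81.0% with 58 df, or 80.0% with 19 df for the pairs and 19 for the controls. At ICC 0.2, SE = 7.86 × √(1.2/40 + 1/20) = 2.223, and power for 6.2 points is about 77%. The variance of the difference rises by 0.080/0.075 − 1 = 6.7%, against 0.055/0.050 − 1 = 10% for 1 vs. 2, because the 20 controls contribute most of it.

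**4. The SD (minor).** If d = 0.64 equals 2.5 and 3.5 points on the subscales, the implied SDs are 2.5/0.64 = 3.906 and 3.5/0.64 = 5.469. At ρ = 0.5 the total SD is √(3.906² + 5.469² + 2 × 0.5 × 3.906 × 5.469) = √66.53 = 8.16. With 8.16 and no clustering, power for 5 points is 77.3% (t, 78 df). The nominal figures would need ρ of about 0.39 to give 7.86. If 2.5, 3.5 and 0.64 are rounded to the last digit shown, the implied SD is 7.96 to 8.36, just above 7.86. If the point values are rounded to the nearest half point, it is about 7.5 to 8.8, which includes 7.86; 2.4 and 3.4 points, for instance, give 7.89.

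**The case against.** The strongest reply is that no ICC is known, so a shortfall cannot be demonstrated, and at low values it is slight: about 2 percentage points at ICC 0.1. The upper end of the range has no support in the documents. One design feature could even reduce the similarity of partners, since the Discussion says that the same partner always starts the exercises, a systematic difference within each pair. The planned analysis already models the pairs, so the test itself is sound. All of this stands. It limits what can be said about the size of the loss, but it does not reconcile a power figure for independent people with a model for pairs.

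A reader might also infer that 7.86 is wrong. The documents do not support that. The subscale differences are given only as approximate, the subscale SDs are not stated, and ordinary rounding could account for the gap to 8.16. Nor is it an error to have assumed ρ = 0.5: the section says openly that the correlation is unknown, so a less favourable value would be a reviewer's preference.

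**Conclusion.** The point holds for pairing. The stated 80% belongs to a design with 40 independent trainees in Group 2, not to the 20 pairs that the plan analyses. It has no reserve, so any positive within-pair ICC brings the power below it. Over an assumed ICC of 0.1 to 0.5 with SD 7.86, power for 5 points is about 78% down to 70%, and the difference detectable with 80% power is about 5.15 up to 5.6 points. The loss is small at the low end and material from about 0.3 upwards. For 2 vs. C it is smaller.

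It would go too far to conclude that the trial is underpowered by a known amount or that its primary test is invalid. The shortfall depends on an ICC that the documents do not give, and the mixed model accounts for the pairs. The SD mismatch is a request for clarification only.

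**What to change.** Keep 40/40/20. In the sample size section, state an assumed within-pair ICC with a range, and restate power and detectable difference for 1 vs. 2 and 2 vs. C on 20 pairs. Suggested wording: with SD 7.86 and an assumed within-pair ICC of 0.2 (range 0.1 to 0.5), power for a 5-point difference between Groups 1 and 2 is about 76% (78% to 70%), and the difference detectable with 80% power is about 5.3 points (5.15 to 5.6); for Group 2 vs. control, power for 6.2 points is about 77% at ICC 0.2. Also give the subscale SDs from which 7.86 was derived, so that it can be reproduced at ρ = 0.5.

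The cost is a few sentences and a slightly less favourable figure. No extra participants are needed, and the analysis model does not change.

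### The 80% power stated for each comparison with Group C ignores the gatekeeper test; under the written two-step rule it is about 75% at d = 0.79 if both trained arms have that effect

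*Protocol article*

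**What the plan says.** The Abstract fixes the design: "A total of 100 students will be randomized into three study arms, in a 2:2:1 ratio", which gives 40, 40 and 20 participants.

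Under Sample size determination, the comparison of the two trained arms is planned first, with "the standard deviation for the total scores of the scales would be 7.86 for both groups". For the comparisons with the control group the text then states: "In each comparison, a standardized effect of d = 0.79 with 80% power can be measured". It also translates this effect into points: "which would represent a mean difference of about 6 points on the OSATS scale". No gatekeeper is mentioned there, and no effect is given for the trained arm that is not in the comparison.

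Under Statistical analysis, the first step is a three-group test of the Group effect. "If the group effect is not significant at α = 5% in this gatekeeper analysis, statistical inference will stop". Only after that: "If the test is significant, all possible pairs of interventions will be compared (1 vs. C, 2 vs. C, 2 vs. 1"), each two-sided at 5% with no further multiplicity adjustment.

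**The concern.** The two sections describe different decision rules. The power figure belongs to one test of two groups. The analysis rule requires two significant results: the three-group test and then the pairwise test. The probability that both are significant cannot exceed the probability that the pairwise test alone is, and it can be clearly lower.

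The gatekeeper does not follow automatically from a real difference between one trained arm and Group C. Its power depends on all three means. It has two numerator degrees of freedom, and it loses sensitivity when the remaining arm lies between the other two.

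The comparisons with Group C are how the trial intends to show that training has an effect (Objectives, Discussion). If one of them is not declared significant, a reader who relies on the printed 80% will credit the design with more sensitivity than its own rule provides.

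**Working it through.** **Inputs from the protocol article.** Group sizes 40/40/20 (Abstract; Sample size determination); two-sided alpha 0.05 for the pairwise tests and 5% for the gatekeeper (Statistical analysis); d = 0.79, about 6 points, and SD 7.86 (Sample size determination).

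**Assumptions added here.** Equal variances, normal scores, independent observations (no correlation within training pairs), and no gender effect. The effect of the other trained arm is not in the document, so it is varied.

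**Step 1: reproduce the printed figure.** For a two-sample t-test the noncentrality is d / √(1/40 + 1/20), with 40 + 20 − 2 = 58 degrees of freedom.
- d = 0.79: 0.79 / √0.075 = 2.885, power 81.0%.
- d = 0.78: power 80.0%.
- 6 points: d = 6/7.86 = 0.763, noncentrality 2.787, power 78.3%.

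So the printed 80% is the power of the single 40 vs. 20 test. Also, 0.79 × 7.86 = 6.2 points, so the figure of about 6 points is rounded down slightly.

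**Step 2: power of the written rule.** Simulation with 1 million draws per scenario. Success for the named arm means that the three-group F-test has p < 0.05 **and** the pairwise t-test against Group C has p < 0.05. The pairwise test here uses the error variance pooled over three groups; using the two compared groups only lowers the results by at most about 0.6 percentage points. The first column is the other trained arm's effect as a multiple of the named arm's effect.

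| Other arm | Gate alone, d = 0.79 | Both tests, d = 0.79 | Both tests, 6 points |
|---|---|---|---|
| 0 | 93.7% | 80.5% | 77.5% |
| 0.25 | 83.7% | 77.0% | 73.8% |
| 0.5 | 74.4% | 72.4% | 69.1% |
| 0.7 | 72.1% | 71.0% | 67.9% |
| 0.75 | 72.6% | 71.3% | 68.1% |
| 1 | 80.2% | 75.4% | 72.2% |
| 1.25 | 90.8% | 79.6% | 76.6% |
| 1.5 | 97.5% | 81.1% | 78.5% |

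With this pooled error term the pairwise test alone has 81.5% power at d = 0.79 and 78.8% at 6 points. With equal arms the gate therefore costs about 6 percentage points at d = 0.79 (81.5 − 75.4 = 6.1).

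**Step 3: effect needed for 80% under the written rule.**
- Equal arms: d = 0.83 gives 80.0%; 0.83 × 7.86 = 6.5 points.
- 1 vs. C with Group 2 at 0.75 of Group 1's effect: d = 0.87 gives 80.3%; 0.87 × 7.86 = 6.8 points. With Group 2 at 0.5, d = 0.86 gives 80.2%.

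**Step 4: chance of finding any training effect.** With both arms at d = 0.79, the gate plus at least one significant comparison with Group C has 80.2% power. The chance of missing any training effect is then about 20%; the chance of missing one named comparison is about 25%.

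**The case against.** The strongest reply has four parts.

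1. **The arithmetic is right for what it describes, and the contrast is not the primary one.** The printed figure reproduces as a per-comparison power. The Objectives make individual vs. paired training the primary goal, and the sample size section expects larger effects against the control group, so d = 0.79 can be read as a lower limit of detectability. This limits the consequence but does not reconcile the two sections: the article prints a power, and its own rule does not deliver it in the equal-arm case.

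2. **The loss depends on means that the plan does not fix.** This stands. Over the scenarios examined, power at d = 0.79 runs from about 71% to 81%. If the planned d = 0.64 also separates the trained arms, the arm at 0.79 has about 78% when the other is at 0.15 and about 81% when the other is at 1.43. A reader might infer that 71-75% is simply the power of the plan, or that the loss disappears only when the trained arms are far apart. Neither is supported. The low end assumes that the other arm gains half to three quarters of the effect, and the Discussion states that no evidence supports the conjecture that pairs do worse. With the other arm at 1.25 times the effect, only about 0.2 SD better (0.25 × 0.79), power is already back near 80%.

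3. **The result at 6 points is partly rounding.** This also stands. The single test has 78.3% there, so only the rest of the shortfall comes from the gate.

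4. **A reader might infer a 25-29% chance of missing that training works at all.** The document does not support that. Its rule ties that conclusion to the gate, and with equal arms at d = 0.79 the chance is about 20%. It reaches about 28% only if the other arm is assumed to gain half to three quarters of the effect, which the plan does not say.

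**Conclusion.** The point holds in a conditional form. The 80% stated for each comparison with Group C belongs to a stand-alone test and leaves out the gatekeeper. Applying d = 0.79 to both trained arms is the most direct reading of a statement about each comparison. On that reading, the power for a named comparison is about 75%, or about 72% at exactly 6 points. A smaller but real effect in the other trained arm lowers it to about 71% (68%). No effect there, or one at least about 1.25 times as large, leaves it near 80% (77-78%).

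These figures assume 40/40/20 analysed participants and independent observations. Correlation within training pairs, for which the article gives no value, would lower 2 vs. C further; that is a separate matter and is not counted here. The finding concerns a stated figure only. It does not invalidate the testing procedure or the sample size.

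**What to change.** In Sample size determination, replace the power claim for the control comparisons with the power of the two-step rule, and state the three group means assumed. For example:

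> Under the gatekeeper procedure, and ignoring pair clustering, each comparison with Group C has about 75% power at d = 0.79 if both trained groups benefit equally; 80% power then requires d of about 0.83 (6.5 points). If Group 2 gains 50-75% of Group 1's effect, 1 vs. C has about 71-72% power at d = 0.79 and needs d of about 0.87 for 80%.

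The second sentence applies to 1 vs. C only and should not be extended to both comparisons. If the effect is also given in points, use 6.2 points for d = 0.79, or give the power at exactly 6 points.

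The cost is a short simulation and a change of wording. No participants are added and the analysis does not change; the stated figure becomes slightly less favourable.

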### Ethical and legal aspects

All data for the study are recorded anonymously, treated confidentially, and are evaluated by authorized staff for scientific purposes only. Participants’ names are kept separate from all study data and are not used for the study. Each participant is assigned a designated code that is used for the entire study documentation and data collection. The study courses are offered in addition to compulsory university courses. Participation in the study is voluntary and may be ended at any time. There are no foreseeable negative consequences for participants related to participation. The participating staff of the Heidelberg MIS center is experienced in the handling of training devices and in tutoring MIS. The benefits of training for students are numerous: stamina, concentration, and manual adroitness are enhanced and practiced, surgical interest may be stimulated or invigorated, and students are able to begin their first practical laparoscopic experience, which may be used during later work. In the event that a participant’s physical or mental health becomes jeopardized due to participation in the present study, the participant will be dismissed immediately and excluded from the study. Ethical approval was obtained by the local ethics committee at Heidelberg University prior to the beginning of the study (Code S-334/2011). Written informed consent is obtained from each trainee.

## Discussion

This study aims to assess the differences in laparoscopy training courses for laparoscopic beginners by using a single workplace to train one or two trainees simultaneously. Since the study participants of Group 2 work in pairs, they repeat each individual exercise less and essentially work for only half of the total training time. Intuitively, this seems disadvantageous, but there is no evidence to support this conjecture. Educating prospective surgeons on common laparoscopic training programs as groups of two might even lead to more successful performances in comparison to solo training. Additionally, this would lead to an effective optimization of resources, as twice the number of trainees could participate in courses.

Despite the careful avoidance of bias, some possible factors of influence still remain, e.g., the contradiction of the high vigilance and motivation of each study participant and the implicated individual difference. Furthermore, it is not ensured that active pauses during exercises always have the same quality for each participant, even though the staff is encouraged to keep making pauses periodically in standardized intervals. We measure if cooperative learning and other exchange effects between the trainees occurs, but not how or why they occur. The expected clinical performance of the study participants will be assessed by the best available simulation, a cadaveric perfused animal organ. Comparison of the two intervention groups will show whether there is a difference in surgical performance based on training alone or in pairs. Comparison of the intervention groups with the control group will show if there exists any training effect at all. The results of the baseline and post-test of the VR trainer should demonstrate the differences in learning success between the trained groups 1 and 2 versus group C without training. The continuous data recording of the VR trainer and the tests will help understand if there is a difference in learning curves between both training groups and between the partners in group 2, as the same training partner always starts the exercises. The assessment of general and individual parameters of the study participants will help understand the possible factors of influence for successful surgical education. As the study is limited to laparoscopically-naive medical students and the performance of basic skills and LC, the results cannot be directly transferred to more experienced surgeons and other interventions. However, the results of this study will increase knowledge about the optimal training conditions for laparoscopic surgery, i.e., if workplaces in surgical training centers should be used by one or two trainees simultaneously in order to achieve the optimal training outcome.

